### Recruitment

Participants will be recruited in primary care settings by participating GPs among patients fulfilling study criteria. When the GP identifies a potential participant, he will explain the patient the characteristics of the study. Whether the patient is interested in participating he/she will sign an informed consent and the GP will fill a document describing the sociodemographic and clinical characteristics of the patient and will give him/her the patients’ information sheet and a handout describing the study. After giving informed consent, subjects will be interviewed in the next 3 days by a researcher. After confirming that have signed the informed consent and understand the study and the treatment options, the researcher will administer psychological tests related with inclusion criteria: MINI International Neuropsychiatric Interview and Beck Depression Inventory II. Patients in the ITAU arm will be allowed to follow psychotherapy program at the end of the study for ethical reasons. Whether the patient fulfills all study criteria, the researcher will administer the remaining baseline tests and will contact an independent researcher to implement randomization.

Recruitment will be done in a consecutive way up to complete sample size and it is expected to take a period of 12 months. Recruitment calculations have been carried out, on conservative bases, according to PREDICT data study [36] that describes a cumulated incidence of depression of 11.5% of the consulting population in primary care. That is to say that for every 1000 non-depressed consulting patients in primary care, 115 will get depressed over 1 year. Since the prevalence of depression is 14%, a GP with a standard consultation made up of 1500 patients, will have 210 patients diagnosed of major depression. From the remaining 1290 non-depressed patients, 148 will get depressed over 1 year, which stands for 2.8 patients a week or 12.3 patients a month. Assuming that every GP will invite 25% of those 12 possible patients and that only 25% will fulfill criteria to participate in the study and will give consent to it, every GP will recruit 1 patient/month during the estimated 12-month recruited period. This allows an estimation of at least 10 GPs for every region (Aragon, Balearic Islands and Andalucía).

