### Sample size

The sample size of this study was based on the expected difference on the primary outcome variable, i.e. depressive symptoms, between the intervention groups and the Treatment as Usual group at post-test. Based on a power of 0.80 in a one-tailed test, an alpha of 0.05, we need 100 subjects in each condition to show an effect-size of 0.40.

Therefore, the total sample size was determined at 300. This sample size also allows calculating clinically significant difference in the main outcome variable, Beck Depression Inventory II. Based on previous studies [36], this difference has been placed at 5 points. It allows changing scoring from normality to mild depression or from mild to moderate depression. Taking account an expected withdrawal rate of 30% according to previous studies [9-14], a sample size of 450 patients (150 by arm) was calculated. The three participating health centers will select 150 patients with cluster randomization to allocate one third in each of the three arms.

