### Randomization, allocation and masking of study groups

Each patient will be allocated to either one of the three groups using a computer-generated random number sequence. We will use block allocation, with 3 blocks (one for each participating region) including 150 patients per block, with about 50 patients per arm. The allocation will be carried out by an independent person, belonging to REDIAPP (Primary Care Prevention and Health Promotion Research Network), who is not involved in the study. The method used to implement the random allocation sequence will be a central telephone. The sequence will be concealed until interventions are assigned. Patients will agree to participate before the random allocation and without knowing which treatment they will be allocated to. Study personnel conducting psychological assessments will be masked to participants' treatment conditions.

The researcher that administers baseline assessments will be unaware of the treatment group to which the patient belongs to. This researcher will be different from the one that administer the questionnaires over the study. GPs will be also unaware, as long as possible, of the arm to which the patient has been randomized, since their treatment should be exclusively based on the recommendations of the guides for the treatment of depression. The flowchart of the study is summarized in Figure 1 (Insert by here).

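### The stated recruitment inputs give about 0.77 patients per GP per month, not 1, and 10 GPs per region do not reach 150 in 12 months at either rate

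*Protocol article*

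**What the plan says.** The Recruitment section gives a chain of figures, described as conservative. The incidence is such that "for every 1000 non-depressed consulting patients in primary care, 115 will get depressed over 1 year". A list of 1500 with 14% prevalence leaves 210 prevalent cases and 1290 patients at risk, and "From the remaining 1290 non-depressed patients, 148 will get depressed over 1 year, which stands for 2.8 patients a week or 12.3 patients a month". The yield is then taken from the incident cases only: "Assuming that every GP will invite 25% of those 12 possible patients", with 25% assumed to qualify and consent. The conclusion is that "every GP will recruit 1 patient/month during the estimated 12-month recruited period", followed by "This allows an estimation of at least 10 GPs for every region".

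The targets stand elsewhere. Under Sample size, "a sample size of 450 patients (150 by arm) was calculated". Under Randomization, allocation and masking of study groups there is one block for each of three regions, "including 150 patients per block, with about 50 patients per arm".

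The Recruitment section expects recruitment to last 12 months, and says that it runs until the sample is reached. Setting and study sample says the same about completing the sample. Forecast execution dates lists recruitment from September 2012 to December 2013.

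**The concern.** The two 25% factors multiply to one sixteenth, and one sixteenth of 12.3 is clearly below 1. Rounding up to a whole patient per month inflates the planned yield by about 30%, in a calculation presented as cautious. The minimum of 10 GPs per region also falls short of the regional target at the rounded rate, so two separate steps fail.

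At stake is the feasibility of the schedule. The GP count determines how many practices must be enlisted and trained, and the recruitment period determines every later date. If both are set from a rate that the inputs do not support, recruitment will overrun or more GPs will have to be found partway through.

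**Working it through.** **Inputs.** From Recruitment: list size 1500; prevalence 14%; annual incidence 11.5% among the non-depressed; 25% invited; 25% of those eligible and consenting; at least 10 GPs in each of 3 regions; 12 months. From Sample size: 450 patients, one-tailed alpha 0.05, effect size 0.40, 30% withdrawal. From Randomization, allocation and masking of study groups: 150 per region. From Forecast execution dates: September 2012 to December 2013, which is 15 or 16 months depending on how the end months are counted.

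**Reproducing the plan's figures.**
- Prevalent cases: 1500 × 0.14 = 210. Agrees.
- At risk: 1500 − 210 = 1290. Agrees.
- Incident cases per year: 1290 × 0.115 = 148.35. Agrees with 148.
- Per week: 148 / 52 = 2.8. Per month: 148 / 12 = 12.3. Both agree.
- Recruits per GP per month: 12.3 × 0.25 × 0.25 = 0.77. **Does not agree with 1.** Using 12 cases a month gives 0.75; the unrounded 12.36 gives 0.773. The overstatement is 1 / 0.77 − 1 = 30%.

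**Expected numbers, with 10 GPs in each of 3 regions.**

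| Rate per GP per month | 12 months, per region | 12 months, total | 15 to 16 months, total |
|---|---|---|---|
| 0.77 (stated inputs) | about 93 | about 278 | about 346 to 371 |
| 1 (stated result) | 120 | 360 | 450 to 480 |
| Target | 150 | 450 | 450 |

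For example, 0.773 × 10 × 12 = 92.7 per region, and × 3 = 278. With 12 cases a month the total is 270. The shortfall at 12 months is (450 − 278) / 450 = 38% at the stated inputs and (450 − 360) / 450 = 20% at 1 per month. The target is met only by combining the rounded-up rate with the longer calendar.

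**What the target would need.**
- GPs per region for 150 in 12 months: 150 / (12 × 0.773) = 16.2, so 17. With 12 cases a month it is 16.7, also 17. At 1 per month, 150 / 12 = 12.5, so 13.
- Months with 30 GPs: 450 / (30 × 0.773) = 19.4, or 450 / (30 × 0.75) = 20.0.

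**Power, only if recruitment were cut off early.** Two-sample t-test, one-tailed alpha 0.05, effect size 0.40, as under Sample size; these inputs need 78 per arm for power 0.80.
- 278 recruited: 278 × 0.70 / 3 = 65 per arm, power about 0.73.
- 360 recruited: 360 × 0.70 / 3 = 84 per arm, power about 0.83.
- 371 recruited (16 months at 0.77): 371 × 0.70 / 3 = 87 per arm, power about 0.84.

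**The case against.** Four things can be said for the plan.

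**Ten is a floor.** The text says at least 10, and nowhere states that 10 GPs deliver 150 or 450 patients; that link is inferred from the target and the expected 12 months. This stands, so the plan is not bound to miss its target. But 10 is the only GP count that the calculation produces, and a minimum that misses the target even at 1 per month is not a useful one.

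**Prevalent cases are left out.** The 210 prevalent patients per GP are counted and then not used. Setting and study sample requires symptoms for more than 2 weeks, not new onset, and does not exclude patients already on antidepressants, so some of them could be recruited. That may be what conservative means here. It stands to this extent: 278 is the yield from incident cases, not a forecast of all recruitment. It does not rescue the figure of 1, because the document applies its percentages only to the monthly incident cases and gives no rate for the rest.

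**The calendar is longer than 12 months.** This narrows the gap at 0.77 but does not close it, and it is itself at odds with the Recruitment section.

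**Recruitment does not stop at 12 months.** A reader might infer that the trial is set to under-recruit and lose its stated power. The documents do not support that: two sections say that recruitment runs until the sample is complete, and 12 months is only an expectation. Nor should two-sided power be used to size a loss of the stated power, since the plan specifies a one-tailed test. Whether that choice is suitable is a separate question.

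**Conclusion.** The arithmetic error holds. The stated inputs give about 0.77 recruits per GP per month (0.75 to 0.77 depending on rounding), not 1, and 10 GPs per region fall short of 150 in 12 months at either rate: about 93 or 120.

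The consequence is for time and resources. With 30 GPs, recruitment would take about 19 to 20 months instead of 12. On the plan's own one-tailed basis, power falls below 0.80 only if recruitment stopped at 12 months with 30 GPs at 0.77, and then to about 0.73. In the other two scenarios examined it stays above 0.80. The validity of the analysis is not affected.

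These figures rest on incident cases only, exactly 10 GPs per region, and the plan's two round 25% assumptions. Prevalent recruits or more GPs would shorten the overrun by an amount that the document gives no means to estimate.

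**What to change.** In the Recruitment section, restate the yield as about 0.77 patients per GP per month, say that it counts incident cases only, and then do one of the following:
- keep 10 GPs per region and restate the recruitment period as about 19 to 20 months; or
- keep 12 months and restate the minimum as about 17 GPs per region (13 would be needed even at 1 per month).

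If the sponsor means to count on prevalent cases, state the rate assumed for them and recompute.

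In either case, reconcile the 12 months with the September 2012 to December 2013 dates in Forecast execution dates, and move the later dates if recruitment is lengthened.

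Correcting the text costs only an edit. The operational cost is either a longer calendar or more participating GPs, each of whom needs the 3-hour training described for improved treatment as usual. At 17 per region that is 51 GPs instead of 30.

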### Randomization, allocation and masking of study groups

Each patient will be allocated to either one of the three groups using a computer-generated random number sequence. We will use block allocation, with 3 blocks (one for each participating region) including 150 patients per block, with about 50 patients per arm. The allocation will be carried out by an independent person, belonging to REDIAPP (Primary Care Prevention and Health Promotion Research Network), who is not involved in the study. The method used to implement the random allocation sequence will be a central telephone. The sequence will be concealed until interventions are assigned. Patients will agree to participate before the random allocation and without knowing which treatment they will be allocated to. Study personnel conducting psychological assessments will be masked to participants' treatment conditions.

The researcher that administers baseline assessments will be unaware of the treatment group to which the patient belongs to. This researcher will be different from the one that administer the questionnaires over the study. GPs will be also unaware, as long as possible, of the arm to which the patient has been randomized, since their treatment should be exclusively based on the recommendations of the guides for the treatment of depression. The flowchart of the study is summarized in Figure 1 (Insert by here).

**Figure 1 F1:**
[figure not shown]
Flowchart of the study: randomization, sampling and monitoring of patients.

### Interventions

#### Internet-delivered psychotherapy

The program “Smiling is fun” is an internet-delivered, multimedia, interactive, self-help program for the treatment of depression, developed by our group based on similar programs in other countries that have demonstrated to be effective [37,38]. The treatment protocol is composed of 8 therapeutic modules and two initial modules (home and welcome). The therapeutic modules are oriented to work on different psychological techniques which will allow the individual to learn and practice adaptive ways to cope with depression and daily problems. Each module includes exercises to practice such techniques. These modules are sequential, in order to move step by step, all along the program. Duration of the program can vary among users, it is estimated that duration for most people will be 3 months. The content of the program is the following:

***M1. Motivation for change*** which aim is to analyze the advantages and disadvantages of changing, emphasizing the importance of being motivated, promoting the individual’s implication to practice and learn all the abilities the program introduces.

***M2. Understanding emotional problems:*** This module provides information to recognize and understand the emotional problems.

***M3. Learning to move on:*** This module focuses on behaviour activation by teaching the importance of “moving on” to acquire a proper level of activity and involvement in life.

***M4. Learning to be flexible:*** This module aims to teach a more flexible way of thinking and to interpret situations, in order to be able to seeing every situation from different perspectives, learning to think about different alternatives.

***M5. Learning to enjoy:*** This module is devoted to teach the importance and performance of positive experiences that generate positive emotions, promoting the involvement in pleasant and significant activities, and contact with other people.

***M6. Learning to live:*** This module involves a further step in the enhancement of positive affect, understanding the importance of identifying the individual’s own psychological strengths and selecting and carrying out meaningful activities linked to values and goals in life.

***M7. Living and learning:*** This module focuses on developing an action plan to boost the individual psychological strengths.

***M8. From now on, what else…?:*** This final module aims to go on and strengthen what has been learnt during the program.

The program recommends working on one module at least for one complete week. The program sends a reinforcing message when the user finishes each module and when the user performs the homework. On the other hand, the program sends an email to the user and to the clinician when more than two weeks between sessions have passed without using it. This message encourages the patient to continue working to benefit of the program.

Patients randomized to this treatment will be given a password to accede to the program at home. An adherence protocol using data from the program will be implemented to know which sessions and homework the patient has done, how much time has taken for every session and psychotherapy technique and the break he has taken in every session. The patients allocated to this intervention will be broken down in two different groups:

*Low intensity Internet-delivered psychotherapy.* Over the treatment period, a researcher trained in psychotherapy will contact with the patients to offer help (asking for any difficulties or problems to fulfil the program), and suggesting to end the therapy within the estimated period. The patient could ask questions or advice to the psychotherapists with a total maximum of <1 hour over the treatment period. They could also ask a technician any problem with the running program in order to solve technological problems.

*Self-guided Internet-delivered psychotherapy.* In this group there will not be any contact with any therapist over the treatment period. Only technical questions about the working of the program could be asked to a technician by mail.

Both groups of patients will receive treatment as usual improved by their GPs, as described in the next paragraph.

#### Improved Treatment as Usual at primary care level (ITAU)

All the patients included in the study (whether they receive psychotherapy or not) will be also treated by their GPs. In practice, ITAU in primary care is any kind of treatment administered by the GP to the patient with depression. However, it can be considered that the Treatment as Usual in primary care will be improved because the participating GP will receive a training program of 3 hours on a widely used Spanish Guide for the Treatment of Depression in Primary Care, which is based on the NICE recommendations for this subject [39]. This Guide describes the use of antidepressants in adequate doses and time of administration. In case of suicide risk, severe social dysfunction or worsening of symptoms, it is recommended to refer the patient to mental health facilities [40].

For the three groups the use of health and social services (health professionals, medications, social workers and other services) will be registered using the CSRI [41].

### Instruments

Patients will be assessed at baseline, posttreatment, and 3 and 12 months after inclusion. The study variables assessed are summarized in Table 1.

**Table 1 T1:** Study variables

**Instrument**	**Assessment area**	**Time of assessment**	**Applied by**
MINI Neuropsychiatric interview [31,32]	Psychiatric diagnosis	Baseline	Researcher A
Beck II Depression Inventory [40,41]	Severity of depression	Baseline and follow-up sessions*	Researcher A (baseline)
			Researcher B (follow-up sessions)
Sociodemographic data	Gender, age, marital status, education, occupation, economical level	Baseline	Researcher A
SF-12 Health Survey [40,41]		Baseline and follow-up sessions*	Researcher A (baseline)
			Researcher B (follow-up sessions)
EQ-5D [42]	Health related quality of life	Baseline and follow-up sessions*	Researcher A (baseline)
			Researcher B (follow-up sessions)
CRSI [43]	Health and social services use	Baseline and follow-up sessions*	Researcher A (baseline)
			Researcher B (follow-up sessions)

Follow-up sessions: Postreatment, 3 and 12 months postreatment.

#### Main outcome

Severity of depressive symptomatology measured by Beck Depression Inventory II [34] using its Spanish validated version [35]. This is one of the most widely instrument used to evaluate severity of depression in pharmacological and psychotherapy trials. This questionnaire has been used because it is recommended to assess depression in primary care patients in which comorbidity with medical disorders is frequent.

#### Secondary outcomes

Socio-demographic variables. The following socio-demographic data will be collected: gender, age, marital status (single, married/relationship, separated/divorced, and widowed), education (years of education), occupation, economical level (in relation with Spanish minimum monthly salary that at the moment of the study was 640€).

Mini-International Neuropsychiatric Interview (MINI). This is a short structured diagnostic psychiatric interview that yields key DSM-IV and ICD-10 diagnoses [42]. MINI can be administered in a short period of time and clinical interviewers need only a brief training. The MINI has been translated and validated in Spanish [43].

EuroQoL-5D questionnaire (EQ-5D – Spanish version) [44]. Generic instrument of health-related quality of life. It has two parts: Part 1 records self-reported problems in each of five domains: mobility, self-care, usual activities, pain/discomfort and anxiety/depression. Each domain is divided into three levels of severity corresponding to no problems, some problems, and extreme problems, which allows obtaining a population-based preference score or societal index (SI). A total of 243 theoretically possible health states can be obtained and the SI is calculated on the basis of these health states. Values range from 1 (best health state) to 0 (death). However, this index may also provide negative values that correspond to health states perceived as worse than death. Utility scores for these health states were assigned using the readily available Spanish population tariffs [45]. Part 2 records the subject's self-assessed health on a VAS, a 10 cm vertical line on which the best and worst imaginable health states score 100 and 0, respectively.

Client Service Receipt Inventory – adapted (CSRI – Spanish version) [41,46]. Questionnaire for collecting information about use of healthcare and social care services and other economic impacts (such as time off work due to illness). The variant used in this study was designed to collect retrospective data on service utilization during the previous months after the last assessment. Data on baseline assess the previous three months before inclusion.

Overall Depression Severity and Impairment Scale [47]**:** OASIS consists of 5 items that measure the frequency and severity of anxiety, as well as level of avoidance, work/ school/home interference, and social interference associated with anxiety. The instructions orient the respondent to considerate wide range of anxiety symptoms (e.g., panic attacks, worries, flashbacks) when answering the questions, and the time frame is “over the past week”. Respondents select among five different response options for each item, which are coded 0–4 and summed to obtain a total score. A psychometric analysis of the OASIS in an undergraduate sample suggested that the scale was unidimensional and has adequate psychometric properties [47].

Overall Depression Severity and Impairment Scale [47]: ODSIS is a self-report measure consists of 5 items. In this case, evaluating experiences related to depression. ODSIS measure the frequency and severity of depression, as well as level of avoidance, work/ school/home interference, and social interference associated with depression. Respondents select among five different response options for each item, which are coded 0–4 and summed to obtain a total score. This instrument can also be used to assess severity and impairment associated with low mood. ODSIS assesses the frequency with which the person has been depressed, the intensity of symptoms, behavioral avoidance and functional impairment associated with depression. So far, there are not published studies examining the psychometric properties of this scale. Norman et al. [47] recommended use and interpret it the same way to the OASIS.

Positive and Negative Affect Scale (PANAS). PANAS [48] consists of 20 items that evaluate two independent dimensions: *positive affect* (PA) and *negative affect* (NA). The range for each scale (10 items on each) is 10 to 50. The instrument’s psychometric properties are quite satisfactory. It has a validated Spanish version [49].

Credibility/expectancy questionnaire [50]. This instrument is a quick and easy-to-administer scale for assessing treatment expectancy and rationale credibility. Credibility has been defined as how believable, convincing, and logical the treatment is, whereas expectancy refers to improvements that clients believe will be achieved [51]. This questionnaire derives the two predicted factors (cognitively based credibility and relatively more affectively based expectancy) that are stable across different populations [52]. The aspects that address these two scales relate to: 1) treatment rationale, 2) treatment satisfaction, 3) degree to which I would recommend to a friend who had the same problem, 4) extent to which is considered to be useful in the same case, 6) extent to which the intervention would be considered aversive. This scale has demonstrated adequate psychometric properties [52]. Our research team has used these scales repeatedly in previous studies with good results [53].

